## Abstract

Hospitalisation in older adults is frequently associated with a significant risk of functional and cognitive decline. This study aims to evaluate the effectiveness of a multicomponent exercise program designed to prevent such declines in acutely hospitalised older adults. The intervention will be implemented across three European hospitals with the goal of enhancing the quality of life and functional independence of this vulnerable population. This study will be conducted as a multicentre, randomised controlled trial with two arms: one group will receive a multicomponent exercise program, while the control group will receive standard care. The intervention will consist of individualised sessions focusing on resistance training, balance, and aerobic exercises over four days during hospitalisation. The primary outcome will focus on functional capacity, which will be assessed using the Short Physical Performance Battery. The primary outcome will be measured at baseline, discharge, and 30- and 90-days post-discharge. In addition to this primary outcome, secondary outcomes will include the Barthel Index, cognitive function assessed through the Mini-Mental State Examination, quality of life measured by the EuroQol-5D-3L, and psychological well-being evaluated using the Geriatric Depression Scale (GDS). Additional metrics will include length of hospital stay and readmission rates within 30- and 90-days post-discharge.

**Trial registration:** ClinicalTrials.gov NCT06634147.

## Introduction

Functional decline among older adults during hospitalisation is a significant concern that affects a substantial portion of this demographic and correlates with adverse prognostic outcomes [1]. Recent research indicates that more than 50% of hospitalised older adults do not recover their pre-admission functional status within one year, leading to increased dependency, higher rates of institutionalisation, and elevated mortality rates [2–5]. This issue persists despite the evidence and recommendations established over 75 years ago [6].

Other than the clinical reason for admission, the observed decline is attributed to several factors, including extended immobilisation, insufficient promotion of physical activity, and disruption of the patient’s daily routine environment, which often emphasises the treatment of acute diseases over the preservation of the patient’s functional abilities. Physical inactivity during hospitalisation not only contributes to the loss of muscle mass, strength, and endurance but is also associated with cognitive decline and an increased incidence of secondary complications [2]. The hospital environment, often characterised by a medical approach favouring bed rest instead of promoting functional recuperation for older inpatients, exacerbates these issues, resulting in a cycle of disability that can lead to irreversible mobility disability.

In hospital settings, standard care practices encompass early mobilisation and physical therapy; however, these interventions frequently prove inadequate for preventing functional decline [7–10]. The limitations of current methodologies are apparent: a shortage of trained personnel to administer structured exercise programs, resource constraints, and a prevailing inclination to keep patients at rest because of concerns about falls. Furthermore, many non-specific rehabilitation programs are characterised by low intensity and are not customised to address the specific needs of older adults, thereby diminishing their efficacy [11].

Our team initially spearheaded a project at a tertiary hospital in Spain [12] which subsequently evolved into a multicentre study at the national level [13]. This project compellingly demonstrated the advantages of implementing an individualised multicomponent exercise program tailored to the specific characteristics and needs of each patient, even during the acute phase of the illness. The accumulated evidence indicates that a more comprehensive and innovative approach, which not only emphasises mobility but also incorporates resistance training and functional exercises adapted to each patient’s individual capabilities, is essential for preserving functional independence and enhancing the quality of life of hospitalised older adults [14–17].

Despite the increasing body of evidence supporting the advantages of exercise in older populations, a significant research gap persists regarding exercise interventions during acute hospitalisation. This study aims to assess the effectiveness of a multicomponent exercise program specifically tailored for hospitalised older adults, suggesting that the implementation of this program would not only enhance functional and cognitive capacities during hospitalisation but also facilitate and improve recovery after discharge, reducing falls, hospital readmission, and costs.

This study endeavours to address the existing gap in the literature regarding the efficacy of structured exercise programmes within the hospital context and their validation in an international setting. Through a rigorously designed intervention, we aim to demonstrate that a proactive approach through exercise can reverse the functional decline associated with hospitalisation, thereby promoting a shift in clinical practice towards a model that prioritises the functional health of older adults in acute care environments.

## Materials and methods

### Trial design

This study will be conducted in accordance with the Consolidated Standards of Reporting Trials [18]. This two-armed, multicentre randomised controlled trial (RCT) will evaluate the effectiveness of a multicomponent exercise program in preventing functional and cognitive decline among hospitalised older adults. The trial will be conducted at three European hospitals: Hospital Universitario de Navarra in Spain (HUN), Hospital Distrital da Figueira da Foz in Portugal (HDFF), and Hospital Nostra Senyora de Meritxell in Andorra (HNSM). A summary of enrolment, interventions and assessments is presented in Fig 1 (SPIRIT schedule), and a flowchart of the participants in Fig 2.

**Fig 1 pone.0332391.g001:**
[figure not shown]
Outline of study as per SPIRIT checklist.

**Fig 2 pone.0332391.g002:**
[figure not shown]
Flow chart of the study.

Eligible subjects will be invited to participate in the trial within 36 h of admission, and the baseline examination will be conducted directly after the inclusion evaluation of the clinical status and stability by the medical team. This trial was registered at ClinicalTrials.gov (NCT06634147). This protocol is reported in accordance with the Standard Protocols Items: Recommendations for Interventional Trials [19]. (S1 File, SPIRIT Checklist).

### Inclusion and exclusion criteria

Participants in this study will be older adults aged 75 years and above who are hospitalised in the Geriatrics and Internal Medicine departments for medical conditions. The inclusion criteria require participants to be able to ambulate with or without assistance, capable of providing informed consent or having a legal representative, and currently hospitalised due to a medical condition. Participation in the study is voluntary, and patients who do not wish to participate will not have their usual medical care affected. Conversely, individuals will be excluded if they have a life expectancy of less than three months, suffer from terminal illnesses, cannot participate in a multicomponent exercise program, exhibit moderate to severe cognitive impairment (Global Deterioration Scale, GDS, stages 6–7), or demonstrate moderate to severe disability (Barthel Index < 60). The eligibility criteria are presented in Table 1. Randomisation will be performed using an online random number generator to ensure the unbiased allocation of participants to the intervention and control groups (randomizer.org).

**Table 1 pone.0332391.t001:** Eligibility criteria.

INCLUSION CRITERIA	• ≥ 75 years old hospitalized in European Geriatrics and Internal Medicine services (HUN, HDFF and HNSM) • Expected hospital stay > 6 days
EXCLUSION CRITERIA	• Refusal to sign the informed consent by the patient/primary caregiver/legal guardian or inability to obtain it. • Life expectancy of less than 3 months or oncologic or non-oncologic disease in terminal phase. • Impossibility of follow-up. • Inability to participate in a multicomponent exercise program. • Medical contraindication to exercise. • Moderate-severe stage neurocognitive disorder GDS – Fast Reisberg 6–7 • Moderate-severe disability (measured by Barthel Index (BI < 60).

### Intervention

Patients in the control group will receive standard care currently provided to all patients, including referrals to physiotherapy as needed. The recruitment start date will be January 2025 in Spain, and September 2025 in Andorra and Portugal, and the expected end date is June 2026. In contrast, the intervention group will participate in a structured multicomponent exercise program, which will encompass progressive and supervised training combining aerobic resistance, strength, and balance over a duration of 4 days during their hospitalisation. The multicomponent training protocol is presented in Table 2. This program will be overseen by trained and experienced professionals on the research team, and upon discharge, participants will receive individualised guidelines for continuing the multicomponent exercise program for three months, along with personalised nutritional recommendations.

**Table 2 pone.0332391.t002:** Multicomponent training protocol.

WARM UP								
Stationary bicycle*						**Chair squats***		
5 min (Borg 3–4)						3 sets x 10 rep.		
RESISTANCE TRAINING*								
Exercises								
Leg press – Seated bench press machine – Leg extension								
PROGRESSION WEIGHT PROTOCOL								
Assessment	**V0**					**V1**	**V2**	**V3**
Session	1RM	**S1***	**S2***	**S3***	**S4***	1RM	1RM	1RM
Sets		2	3	3	3			
Repetition		10	10	10	8			
(% 1RM)		40	50	60	70			
Rest (sec)		120 between sets and exercises						
BALANCE: Core and Hip stability*								

***Only Intervention Group.**

**V0: visit 0; V1: visit 1; V2: visit 2; V3: visit 3; S1: session 1; S2: session 2; S3: session 3; S4: session 4.**

The multicomponent exercise program will include chair squats (sit-to-stand exercise). The main training phase will use machines for strength training targeting major muscle groups: the lower extremities (such as leg press and knee extension) and one exercise for the upper extremities (seated chest press). The objective is to perform 2–3 sets of 8–10 repetitions at an intensity of 40–70% of one repetition maximum (1RM), tailored to everyone’s functional capacity. Each training session will also incorporate hip abduction exercises, balance exercises, and stretching routines, ensuring a comprehensive approach to enhance health and mobility among participants. A daily logbook will be used during the hospital stay to register the exercise sessions performed for the intervention group, as well as treatment safety.

Patients will be followed up for 3 months, and there will be coordination between the exercise program in the hospital and primary care (Fig 3).

**Fig 3 pone.0332391.g003:**
[figure not shown]
Schematic study timeline.

### Data collection

Data will be systematically collected at four distinct time points to evaluate the intervention effects. Initially, at admission, a comprehensive assessment will be conducted to establish baseline measures of functional capacity, cognition, nutritional status, and quality of life. Following this, at discharge, the same variables will be re-evaluated to determine any immediate changes resulting from the intervention. Additionally, follow-up assessments will be performed at one- and three-months post-discharge to monitor longitudinal changes in functional capacity, cognition, quality of life, and to document any adverse events, including falls and readmissions. This structured approach aims to provide a robust dataset for analysing the efficacy of the intervention over time.

The **primary outcome** of the study focuses on the functional capacity of older adults, assessed through the Short Physical Performance Battery (SPPB), with evaluations occurring at discharge, one month, and three months post-discharge compared to baseline. The SPPB consists of three essential components: standing balance, walking speed, and the 5 times chair stand test, which assesses lower extremity strength and endurance. This tool has been rigorously validated in older adults experiencing frailty, demonstrating high sensitivity to changes in their physical function. Furthermore, the SPPB is a reliable predictor of various clinical outcomes, making it a valuable instrument for evaluating the functional capabilities of older adults [20]. **Secondary outcomes** encompass a variety of health-related variables, including changes in Barthel Index [21] scores and the percentage of functional recovery after hospitalization. Additionally, cognitive variables such as the Mini-Mental State Examination (MMSE) [22] and the Trail Making Test A (TMT-A) [23] will be assessed from baseline to discharge, and at one and three months. Changes in affective status (GDS), [24] number of medications, fall frequency, mortality, hospital readmissions, quality of life (EuroQoL-5D-3L) [25], maximum isometric strength (HandGrip), and maximum dynamic strength in the upper and lower limbs will also be assessed, along with the average length of hospital stay and changes in sleep quality (SATED scale) [26] at discharge, at one month, and at three months. The assessment times for the different variables are shown in Table 3.

**Table 3 pone.0332391.t003:** Time of assessment of different variables in the trial.

MEASUREMENT	DURING HOSPITALIZATION	AFTER DISCHARGE		
	Visit 0	Visit 1	Visit 2	Visit 3
	(inclusion)	(discharge)	(1 month)	(3 month)
**Sociodemographic information**	**x**			
**Height and weight**	**x**		**x**	**x**
**Adverse events**		**x**	**x**	**x**
**Previous lifestyles questions (Alcohol, tobacco..)**	**x**			
**Mini nutritional assessment (MNA-30)**	**x**			
**SARC-F**	**x**			
**Barthel Index**	**x**	**x**	**x**	**x**
**Short Physical performance Battery (SPPB)**	**x**	**x**	**x**	**x**
**Test 1RM**	**X**	**X**	**X**	**X**
**HandGrip**	**x**	**x**	**x**	**x**
**Linda fried frailty**	**x**			
**Mini-Mental State Examination (MMSE)**	**x**	**x**	**x**	**x**
**Trail Making Test Part a (TMT-A)**	**x**	**x**	**x**	**x**
**Yesavage Geriatric Depression Scale (GDS-15)**	**x**	**x**	**X**	**X**
**Delirium 4AT**	**x**	**x**		
**Reisberg Scale (GDS)**	**x**			**x**
**Quality of life (EQ-5D-3L)**	**x**		**x**	**x**
**SATED Scale**	**x**	**x**	**x**	**x**
**Cumulative Illness Rating for Geriatrics (CIRS-G)**	**x**			
**Polypharmacy**	**x**			
**Falls**	**x**	**x**	**x**	**x**
**Personal history and other geriatric syndromes. Diseases considered grouped by CIE-10 codes and by Salisbury ACG codes.**	**x**			

Peripheral blood (PB) samples will be obtained from all patients at baseline (V0), at discharge (V1), and at 90 days (V3) to obtain serum, plasma, and buffy coat after centrifugation in a fixed-angle rotor at 3,300 *rpm* for 10 min at room temperature. Samples will be divided into 100 μL aliquots and immediately stored at −80°C.

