### Statistical methods

First, a comprehensive descriptive analysis will be conducted on the entire sample and within individual groups. For continuous variables, measures of central tendency and dispersion will be calculated based on their distribution, utilising either the mean and standard deviation or the median and interquartile range (IQR). Qualitative variables will be summarised as frequencies and percentages, with corresponding confidence intervals to estimate the overall prevalence. Baseline characteristics between the treatment and control groups will be compared using the Student’s t-test or the Mann–Whitney U test for quantitative variables, and the Chi-square test or Fisher’s exact test for qualitative variables.

The impact of the intervention on various outcome measures will be assessed using ANCOVA or linear mixed-effects models with a random intercept for continuous variables. Logistic regression models and analyses of rate or proportion differences will be applied to outcomes such as falls, mortality, and institutionalisation. In the event of significant baseline imbalances in any independent variable, sensitivity analyses will be conducted to adjust for these differences in the final analysis. No imputation of missing data will be conducted.

The analysis will adhere to the intention-to-treat principle, and additional per-protocol analyses will be performed as a secondary sensitivity measure. Statistical significance will be determined at a threshold of 0.05 for all tests. Data analysis will be conducted using SPSS (version 25.0) and R software (version 4.0).

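### Table 3 schedules no discharge EQ-5D-3L and no post-baseline medication record, although the outcome text calls for both

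*Protocol article*

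**What the plan says.** The Data collection section of the protocol article describes admission as giving "baseline measures of functional capacity, cognition, nutritional status, and quality of life". It then says that "at discharge, the same variables will be re-evaluated to determine any immediate changes resulting from the intervention". For the 1- and 3-month visits it names functional capacity, cognition and quality of life, and drops nutritional status.

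The secondary outcomes follow. One sentence begins "Changes in affective status (GDS), [24] number of medications", and its list includes "number of medications, fall frequency, mortality, hospital readmissions, quality of life (EuroQoL-5D-3L) [25". It ends with sleep quality and the three times discharge, one month and three months. The section then refers the reader to Table 3 for assessment times.

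In Table 3:
- the row "Quality of life (EQ-5D-3L") is marked at Visit 0, Visit 2 and Visit 3, with Visit 1 (discharge) blank;
- the row "Polypharmacy" is marked at Visit 0 only, and no other row concerns medication;
- the Mini Nutritional Assessment is marked at Visit 0 only.

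The Statistical methods section applies logistic regression and rate or proportion differences to "outcomes such as falls, mortality, and institutionalisation". Institutionalisation is not in the secondary outcome list and has no row in Table 3.

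**The concern.** The text and the table give different instructions on what to collect, and sites will normally work from the table.

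Quality of life is a named secondary outcome in the Abstract as well as in Data collection, and discharge is the visit meant to show the immediate effect of the in-hospital programme. A patient-reported score not taken at discharge cannot be reconstructed later. The plan rules out imputation, and a mixed model cannot estimate a treatment difference at a visit where nobody was measured.

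The medication outcome is affected more completely. A variable recorded only at inclusion precedes any effect of the programme, so it describes the sample and cannot serve as an outcome.

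Recruitment is staggered (Spain from January 2025, Andorra and Portugal from September 2025), so an unclear schedule also leaves room for sites to collect different data.

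**Working it through.** No figure in the plan bears on this point. The only computed figure is the sample size, which uses SPPB inputs alone (difference of 1 point, SD 2.5, correlation 0.5). The check is therefore a comparison of the text with Table 3.

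**Step 1: the four domains said to be measured at admission and again at discharge.**

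| Domain in the text | Table 3 instrument | V0 | V1 (discharge) | V2 | V3 | Agrees at discharge? |
|---|---|---|---|---|---|---|
| Functional capacity | SPPB, Barthel Index | x | x | x | x | Yes |
| Cognition | MMSE, TMT-A | x | x | x | x | Yes |
| Quality of life | EQ-5D-3L | x | blank | x | x | No |
| Nutritional status | Mini Nutritional Assessment | x | blank | blank | blank | No |

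Two of the four domains agree and two do not.

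**Step 2: is the blank cell a fault in reading the table?** Probably not. Other rows keep their empty cells in place: height and weight is also blank at Visit 1, and adverse events is blank at Visit 0.

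**Step 3: number of medications.** The only medication row has one mark, at Visit 0. If the opening word of the outcome sentence (changes) governs the whole list, the outcome needs a baseline and at least one later value. If it governs only the depression scale, the outcome still needs a value after randomisation. Both readings fail with a single baseline record.

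**Step 4: count of scheduled post-baseline visits.**
- EQ-5D-3L: 2 of 3 (1 month and 3 months), so 3 − 2 = 1 is missing, at discharge.
- Medication: 0 of 3, so all 3 are missing.

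**Step 5: institutionalisation.** It is named for analysis in Statistical methods, absent from the outcome list in Data collection, and has no row in Table 3 and no stated source. Mortality, readmissions and length of stay also have no row of their own, yet all three are listed outcomes, and the text places readmissions with adverse events at follow-up. A missing row therefore does not show that the data are not collected. What the documents do show is that an analysed outcome is not listed as one.

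**The case against.** The best defence is that the text itself hands assessment times to Table 3. On that view the sentence about repeating the same variables at discharge is a loose summary, the table governs, and an article condenses a fuller protocol anyway. This has force, but it only decides which side to correct. For quality of life and nutrition the article states both sides and they disagree. For medications, letting the table govern leaves a secondary outcome with no outcome data scheduled.

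Several stronger readings are tempting, and the documents do not support them:
- **EQ-5D-3L cannot be analysed.** It can, at 1 and 3 months. Only the discharge comparison is lost.
- **The text promises every listed outcome at all three later times.** The closing time phrase comes directly after the sleep scale and may govern only that. The EQ-5D-3L conflict rests on the separate sentence about discharge.
- **Medication data are lost for good.** Counts may be recoverable from charts or prescription records, although the article names no such source.
- **Institutionalisation is a secondary outcome with no data.** It is not listed as an outcome, and the missing row proves nothing about collection (step 5).
- **Nothing on nutrition is followed up.** Height and weight are scheduled at Visits 2 and 3, and nutritional status is not a listed secondary outcome.
- **Registered outcomes would be dropped silently.** The registry record is not at hand, and the Trial status section undertakes to report deviations.

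**Conclusion.** The point holds for two secondary outcomes. Under Table 3 as written, EQ-5D-3L has no discharge value for any patient, so one of its three post-baseline comparisons cannot be made. Number of medications has no scheduled post-baseline value, so none of its three can be made from scheduled data. The nutritional mismatch at discharge and the unlisted institutionalisation outcome are minor points of wording.

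This rests on three assumptions: that sites follow Table 3; that the Polypharmacy row is where the medication count is recorded; and that no other schedule adds these assessments. Fig 1, the SPIRIT schedule, could not be read for this check and should be compared with Table 3.

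The effect is confined to secondary outcomes, but it is worth settling promptly, because each discharge without an EQ-5D-3L makes that gap permanent for that patient.

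**What to change.** Choose one of two routes for each item and make the text and table agree.

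- **Collect it.** Add EQ-5D-3L at Visit 1 and a medication count at Visits 1 to 3, taken from the chart or prescription record, to Table 3 and the case report form. The cost is a few minutes per visit. For patients already discharged, the medication count may be filled in from records but the discharge EQ-5D-3L cannot; the report should then state how many patients the discharge comparison covers.
- **Or correct the text.** State in Data collection that EQ-5D-3L is assessed after baseline at 1 and 3 months only, and that number of medications is a baseline descriptor, removing it from the secondary outcomes. This costs only the wording change.

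In the same edit, describe nutritional status as baseline only, unless the Mini Nutritional Assessment is wanted at discharge. Either list institutionalisation as an outcome with its data source or remove it from Statistical methods.
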